### Part B.

Subjects in Part B of the study will be randomised to one of the following sequences: E F E F, F E F E, E F F E or F E E F in a 1:1:1:1 ratio where one of these will be placebo and the other will be SB705498. The first letter in the sequence will be applied to the first application site as shown in [Figure 3](#). Each subsequent letter will be applied to the next application site. This ensures that the dose of SB705498 will be compared to placebo on the same area of the opposite forearm for both the histamine and cowhage test.

**Figure 3 Example Schematic of application Sites****Part A**[figure not shown]**Part B**[figure not shown]

\*Note: The days on which the Cowhage and Histamine challenges will take place are interchangeable.

### 4.3. Investigational Product and Other Study Treatment Dosage/Administration

|                                               | Study Treatment                            |                                            | Challenge Agent                                                       |                                                            |                                                                                                   |
|-----------------------------------------------|--------------------------------------------|--------------------------------------------|-----------------------------------------------------------------------|------------------------------------------------------------|---------------------------------------------------------------------------------------------------|
| Product name:                          | SB705498                            | Placebo                             | Cowhage                                                        | Capsaicin                                           | Histamine                                                                                  |
| Dosage form:                           | Cream                                      | Cream                                      | Spicules                                                              | Cream                                                      | Solution                                                                                          |
| Unit dose strength(s)/Dosage level(s): | 1%, 3% and 5%                              | Placebo                                    | 30-35 spicules                                                        | 0.075%                                                     | 1% (10mg/mL)                                                                                      |
| Route/ Administration/ Duration:       | Topical/cream/ 1 hour                      | Topical/cream/ 1 hour                      | Pierce Superficial layer of skin/ spicules/ 15 mins                   | Topical/Cream/ 30mins                                      | Pierce Superficial layer of skin/Solution /N/A                                                    |
| Dosing instructions:                   | Apply cream to designated area as directed | Apply cream to designated area as directed | Gently rubbed onto designated area of skin as directed in Section 7.3 | Apply cream to designated area as directed in Section 7.3. | 1% solution of histamine will be applied using the skin prick method as described in Section 7.3. |
| Physical description:                  | White to slightly coloured, opaque cream.  | White to slightly coloured, opaque cream.  | 2mm brown fibres                                                      | White to slightly coloured, opaque cream.                  | Clear liquid                                                                                      |
| Manufacturer/ source of procurement:   | GSK                                        | GSK                                        | External academic lab                                                 | Cephalon                                                   | ALK Abello                                                                                        |
| Method for individualizing dosage:     | Use of pipette from single use container   | Pipette from single use container          | 30-35 spicules counted out into individual single use container       | Single use syringe from single use container               | Individual drops with single use lancet for piercing                                              |

### 4.4. Dose Adjustment/Stopping Criteria

The systemic exposure associated with the proposed topical dose of SB705498 is not known prior to study start but is expected to be low. The proposed topical dose for this study is a maximum of 95 mg across both parts. Given that SB705498 has been administered as single oral doses up to 1000mg and intranasally up to 12mg twice daily for 14 days, the dose for this study has substantial safety margins and is therefore not expected to require any dose adjustment.

#### 4.4.1. Dose Adjustment/Stopping Safety Criteria

##### 4.4.1.1. Liver Chemistry Stopping Criteria

Liver chemistry threshold stopping criteria have been designed to assure subject safety and to evaluate liver event etiology (in alignment with the FDA premarketing clinical liver safety guidance). Study treatment will be stopped and the subject withdrawn from the study if any of the following liver chemistry stopping criteria is met in either session:

1. ALT  $\geq$  3xULN and bilirubin  $\geq$  2xULN (or ALT  $\geq$  3xULN and INR^1 > 1.5) NOTE: serum bilirubin fractionation should be performed if testing is available. If fractionation is unavailable, urinary bilirubin is to be measured via dipstick (a measurement of direct bilirubin, which would suggest liver injury).

1. INR testing not required per protocol and the threshold value does not apply to subjects receiving anticoagulants.

2. ALT  $\geq$  5xULN.
3. ALT  $\geq$  3xULN if associated with the appearance or worsening of rash or hepatitis symptoms (fatigue, nausea, vomiting, right upper quadrant pain or tenderness, fever, rash or eosinophilia).
4. ALT  $\geq$  3xULN persists for  $\geq$  4 weeks.
5. ALT  $\geq$  3xULN and cannot be monitored weekly for 4 weeks. Subjects with ALT  $\geq$  3xULN **and** < 5xULN **and** bilirubin < 2xULN, who do not exhibit hepatitis symptoms or rash, can continue study treatment as long as they can be monitored weekly for 4 weeks.

**Refer to Section 14, Liver Chemistry Follow-up Procedures, for details of the required assessments if a subject meets any of the above criteria.**

##### 4.4.1.2. QTc Withdrawal Criteria

- QTc, QTcB, QTcF > 500 msec or uncorrected QT > 600 msec
- Prolongation of QTcB or QTcF by > 60 msec as compared to baseline
- If subject has underlying bundle branch block then the QTc withdrawal criteria depends on the baseline value:

| Baseline QTc value (with underlying bundle branch block) | QTc withdrawal criteria |
|----------------------------------------------------------|-------------------------|
| <450 ms                                                  | >500 ms                 |

Withdrawal decisions are to be based on an average QTc value of triplicate ECGs. If an ECG demonstrates a prolonged QT interval, obtain 2 more ECGs over a brief period, and then use the averaged QTc values of the 3 ECGs to determine whether the subject should be discontinued from the study. Subjects who are withdrawn, will not return for a second session.

**4.4.2. Stopping Criteria**

The results from Part A will be reviewed to determine if Part B of the study will be conducted. If no effect is observed in Part A, then the study may be stopped for futility.

If more than 2 subjects are withdrawn due to severe skin reactions as result of study procedures a safety review will be triggered and no further dosing will take place pending this review. If an SAE is reported as possibly related to the study drug, the study will be put on hold pending a safety review.

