### 5.2.2. Exclusion Criteria

Deviations from exclusion criteria are not allowed because they can potentially jeopardise the scientific integrity of the study, regulatory acceptability or subject safety. Therefore, adherence to the criteria as specified in the protocol is essential.

A subject will not be eligible for inclusion in this study if any of the following criteria apply:

1. Suffers from skin infection or inflammation of the forearm, or has other arm skin irregularities that may in the opinion of the investigator interfere with study assessments (e.g. nevi, tattoos).
2. The subject suffers from eczema, psoriasis or any other acute or chronic dermatological problem if, in the opinion of the investigator this is likely to interfere with study assessments

3. Any subject with localised sunburn in the area to be treated as part of the study.
4. History of regular alcohol/drug consumption within 6 months of the study. Regular alcohol consumption defined as: an average weekly intake of >21 units for males and >14 units for females. One unit is equivalent to 8 g of alcohol: a half-pint (~240 ml) of beer, one glass (125 ml) of wine or one (25 ml) measure of spirits.
5. A positive pre-study drug/alcohol screen at screening visit. A minimum list of drugs that will be screened for include amphetamines, barbiturates, cocaine, opiates, cannabinoids and benzodiazepines.
6. The subject has participated in a clinical trial resulting in exposure to more than four new chemical entities within 12 months prior to the first dosing day or has received an investigational product within the following time period prior to the first dosing day in the current study: 90 days, 5 half-lives or twice the duration of the biological effect of the investigational product (whichever is longer).
7. Unable to refrain from use of prescription or non-prescription drugs. Refer to Section 9 for details.
8. History of sensitivity to any of the study medications SB705498, challenge agents or components thereof or a history of drug or other allergy that, in the opinion of the investigator or GSK Medical Monitor, contraindicates their participation.
9. Where participation in the study would result in donation of blood or blood products in excess of 500 mL within a 56 day period following completion of the study.
10. Lactating females.
11. A positive pre-study Hepatitis B surface antigen or positive Hepatitis C antibody result within 3 months of screening

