### **10.3.1. Subject Withdrawal from Study**

Subjects will be withdrawn if they experience:

- An intercurrent illness that is considered to compromise either their safety and well-being or the scientific validity of the study Unacceptable AEs
- A change in status with regard to exclusion criteria
- A subject may voluntarily discontinue participation in the study at any time. The Investigator may also, at his or her discretion, discontinue the subject from participating in the study at any time.

Decision regarding replacement of subjects prematurely discontinued from study will be made by the Investigator and GSK Medical Monitor on a case-by-case basis.

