### **10.3.2. Subject Withdrawal from Study Treatment**

A subject will be considered to have prematurely withdrawn if he/she does not complete dosing for the entire planned treatment period for his group, having received the first dosing, for any reason. Once a subject has discontinued study drug, the subject may not re-enter the study.

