### **13.5. Evaluating AEs and SAEs**

#### **13.5.1. Assessment of Intensity**

The investigator will make an assessment of intensity for each AE and SAE reported during the study and will assign it to one of the following categories:

Mild: An event that is easily tolerated by the subject, causing minimal discomfort and not interfering with everyday activities.

Moderate: An event that is sufficiently discomforting to interfere with normal everyday activities.

Severe: An event that prevents normal everyday activities.

An AE that is assessed as severe will not be confused with an SAE. Severity is a category utilized for rating the intensity of an event; and both AEs and SAEs can be assessed as severe. An event is defined as ‘serious’ when it meets at least one of the pre-defined outcomes as described in the definition of an SAE.

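### The skin-reaction pause in Section 4.4.2 counts withdrawals, so severe non-serious reactions first seen after a subject's last application may leave the trigger unmet

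*Protocol*

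**What the plan says.** Section 4.4.2 contains two automatic study-level safety triggers. The first is for skin: "If more than 2 subjects are withdrawn due to severe skin reactions as result of study procedures a safety review will be triggered", with dosing stopped until the review is done. The second puts the study on hold for a single SAE reported as possibly related to the study drug.

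Withdrawal is described in two places. Section 10.3.2 treats a subject as prematurely withdrawn from treatment if he or she "does not complete dosing for the entire planned treatment period". Section 10.3.1 lists grounds for withdrawal from the study. Two are relevant here: unacceptable adverse events, run into the end of the first bullet ("the scientific validity of the study Unacceptable AEs"), and "A change in status with regard to exclusion criteria".

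Section 13.5.1 separates severity from seriousness: "An AE that is assessed as severe will not be confused with an SAE". Section 10.1 makes a subject a completer only once the follow-up visit has been attended. The Time and Events tables (Sections 4.5.1 and 4.5.3) place that visit 10 to 14 days after the last dose.

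**The concern.** A pause rule should respond to the event it guards against. This one responds to an administrative consequence of the event. During dosing the two will often coincide. After the last planned application they can separate, because stopping treatment is no longer an available response.

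What is at stake is the dosing of other subjects. If severe reactions appear late in subjects who have finished, the rule should prompt a review before more people are dosed, whether later entrants to Part A or subjects in Part B. Section 1.3 says there are no clinical data yet on the topical form, so the trial cannot draw on human experience of how its skin reactions behave over time.

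**Working it through.** There is no stated operating characteristic to reproduce. The check is a reading of the rule followed by a count.

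**Inputs**
- Threshold: more than 2 subjects withdrawn (4.4.2), so at least 3.
- Planned numbers: 16 in Part A and 10 in Part B, the latter drawn from Part A where possible (5.1).
- Applications: four over two days in each part (footnotes to 4.5.1 and 4.5.3).
- After dosing: a brief physical examination at follow-up (4.5.1, 4.5.3), which includes the skin (7.2).

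**Which routes lead into the count after the last application?**
1. *Withdrawal from treatment (10.3.2).* Closed. Dosing is complete, so the definition cannot be met.
2. *Withdrawal from the study for an unacceptable adverse event (10.3.1).* Open until follow-up. The term is not defined and is not tied to the severe grade.
3. *Withdrawal for a change in exclusion status (10.3.1).* Open. Exclusion 1 in Section 5.2.2 begins "Suffers from skin infection or inflammation of the forearm". It goes on to refer to the investigator's opinion about interference with assessments, and it is unclear whether that qualifies the whole criterion. If it does, little remains to interfere with once the challenges are over.
4. *The SAE hold.* It does not reach a severe reaction that is not serious (13.5.1).

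No section makes a severe skin reaction a mandatory reason for withdrawal. For reactions to the challenge agents, Sections 1.7.2 to 1.7.4 leave withdrawal from treatment to be used where needed.

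**Who is affected?** Subjects going on to Part B still have dosing ahead after Part A, so they can be withdrawn and counted at that stage. The gap therefore concerns mainly the Part A subjects who do not continue (16 − 10 = 6 at planned numbers) and the Part B subjects after their final application.

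**The count.** Suppose three subjects have a severe, non-serious reaction first seen after their last application, and *k* of them are also withdrawn from the study.

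| *k* | Count under 4.4.2 | More than 2? | Count if reactions are counted |
|---|---|---|---|
| 0 | 0 | no | 3 |
| 1 | 1 | no | 3 |
| 2 | 2 | no | 3 |
| 3 | 3 | yes | 3 |

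The pause fires only if all three are withdrawn. For scale, three subjects are 3/16 = 18.8% of planned Part A or 3/10 = 30% of planned Part B. The rule itself sets no separate count by part, and replacement or additional subjects are allowed (5.1).

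**The case against.** The strongest reply is that the rule is clear and that a miss needs an unlikely combination. Severe means that ordinary daily activity is prevented (13.5.1). An investigator who grades a reaction to cream on a 3 × 3 cm patch that way would probably also call it unacceptable and withdraw the subject, and Section 4.4.2 does not restrict withdrawal to withdrawal from treatment. At least three subjects would have to be affected. Section 1.2 describes the rabbit skin findings as non-adverse and reports no sensitisation in the mouse assay. An important medical event can be judged serious (13.2), and one such case, if possibly drug-related, stops the study. Adverse events are collected to follow-up (13), Part A is reviewed before Part B (4.4.2), and the sponsor may suspend at any time (15.5).

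Most of this stands and narrows the point. It makes a miss less likely, but none of it makes the numeric rule count the event.

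The reply also warns that capsaicin, histamine and cowhage are meant to provoke the skin or itch, and that requiring withdrawal filters out intended effects. That is fair and is met in the fix. It is limited because the severe grade is demanding and the present rule already covers study procedures.

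A reader might infer three stronger things that the documents do not support:
- *That late severe reactions can never count, or go unmonitored.* Section 10.3.1 leaves a route open, and adverse-event review continues.
- *That the skin rule contradicts the liver rule.* Section 4.4.1.1 says "Study treatment will be stopped and the subject withdrawn from the study if any of the following liver chemistry stopping criteria is met". That is a rule for the individual subject with no study-level count, so the difference is not an inconsistency.
- *That a loss in trigger probability can be calculated.* The protocol gives no severe-reaction rate, onset time or withdrawal practice. Any such figure would rest on invented inputs, and treating every late reaction as uncounted would ignore Section 10.3.1.

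**Conclusion.** The point holds in a limited form. The only prespecified skin trigger depends on a withdrawal decision that, after the last planned application, is partly discretionary and has no treatment left to stop for that subject. Three severe, non-serious late reactions could therefore leave it unmet, with a count anywhere from 0 to 3.

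The likelihood cannot be estimated. The conclusion assumes only that the reactions are not serious, that the affected subjects have no further planned dosing, and that at least one of them is not withdrawn from the study before follow-up. The missed pause has practical consequences only while other subjects remain to be dosed. The protocol itself allows for slow recruitment (4.1.2, 6.2.3). This is a gap in one rule, not in safety oversight as a whole, and it is worth closing because the change is small.

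**What to change.** Amend Section 4.4.2 so that the review is triggered when more than 2 subjects have a severe skin reaction, with these terms:
- severity graded by Section 13.5.1;
- judged by the investigator to result from study treatment, a challenge agent or another study procedure;
- occurring from the first application of a challenge agent or study cream up to the follow-up visit;
- counted whether or not the subject is withdrawn;
- excluding the expected transient flare, wheal, burning or itch of a challenge that resolves as anticipated.

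This needs little new data. Adverse events are already collected to follow-up, and Section 13.5.1 provides that "The investigator will make an assessment of intensity for each AE and SAE reported during the study". Section 13.5.2 asks for causality against study treatment only, so attribution to a challenge agent or procedure should be recorded for severe skin reactions. The present rule already implies that judgement. The downside is an occasional extra safety review with a temporary pause in dosing.

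A minor companion change would extend the automatic SAE hold in the same section from the study drug to challenge agents and study procedures. It is less pressing, because 24-hour SAE reporting (13.7) and urgent safety measures (15.2.1) already apply.

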## 4.5. Time and Events Table

### 4.5.1. Part A

| Procedure                                             | Screening
(up to 30 days
prior to Day
1)- May be
split over 2
days | Study Day (per treatment arm) |                |                |                |         | Follow-up

(10-14 days
post-last
dose) |
|-------------------------------------------------------|-----------------------------------------------------------------------------------|-------------------------------|----------------|----------------|----------------|---------|----------------------------------------------------|
|                                                       |                                                                                   | -30 min                       | Day 1 and 2    |                |                |         |                                                    |
|                                                       |                                                                                   |                               | 0              | 60 min         | 95 min         | 120 min |                                                    |
| Admission to Unit                                     | X                                                                                 | X                             |                |                |                |         |                                                    |
| Informed Consent                                      | X                                                                                 |                               |                |                |                |         |                                                    |
| Full Physical Exam                                    | X                                                                                 |                               |                |                |                |         |                                                    |
| Brief Physical Exam                                   |                                                                                   |                               |                |                |                |         | X                                                  |
| Medical/medication/
drug/alcohol history           | X                                                                                 |                               |                |                |                |         |                                                    |
| Vital signs                                           | X                                                                                 | X                             |                |                |                |         | X                                                  |
| ECG                                                   | X                                                                                 | X                             |                |                |                |         | X                                                  |
| Urine Drug/Alcohol                                    | X                                                                                 | X                             |                |                |                |         |                                                    |
| Serum β-hCG (women)- Day 1 only                       | X                                                                                 | X                             |                |                |                |         | X                                                  |
| HIV, Hep B and Hep C screen-                          | X                                                                                 |                               |                |                |                |         |                                                    |
| Haem/Chem/Urinalysis tests                            | X                                                                                 |                               |                |                |                |         | X                                                  |
| Administration of SB705498 cream/Placebo  |                                                                                   |                               | X              |                |                |         |                                                    |
| Assess area of flare using LDI                        | X                                                                                 |                               | X  | X  | X  | X       |                                                    |
| Capsaicin challenge                                   | X                                                                                 |                               |                | X              |                |         |                                                    |
| Histamine/Cowhage Challenge                           | X                                                                                 |                               |                |                |                |         |                                                    |
| Assess ITCH intensity (COVAS)                         | X                                                                                 |                               |                |                |                |         |                                                    |
| Adverse Event Review                                  | X                                                                                 | ←=====→                       |                |                |                |         | X                                                  |
| Concomitant Medication Review                         | X                                                                                 | ←=====→                       |                |                |                |         | X                                                  |
| Pharmacokinetic sample                                |                                                                                   |                               | X              | X              | X              | X       |                                                    |
| Discharge                                             |                                                                                   |                               |                |                |                |         | X                                                  |

1. Baseline scan will be performed before application of the SB705498 cream or Placebo
2. LDI scan will be performed after application of SB705498 cream or placebo. Cream is applied, left for 1 hr and excess is then removed to allow scanning.
3. LDI scan will be performed 5 mins after the Capsaicin cream is wiped off the arm.
4. Application of the cream/placebo followed by capsaicin challenge and LDI scanning will be performed twice on each day. i.e. 4 applications over the 2 days with the 3 different doses of SB705498 and placebo.

